#### Process evaluation

A mixed-methods approach will examine the elements of the conceptual framework for implementation outcomes^25^ as they relate to the PCEssentials intervention, namely: acceptability, adoption, appropriateness, penetration, feasibility, fidelity and sustainability. To assess programme acceptability and feasibility, clinical stakeholders involved in the delivery or oversight of the programme will be invited by the partner investigator at each site to participate in (1) a short online survey when recruitment commences and ends at the site and (2) a semistructured interview when recruitment ends. Invitations will be sent to eligible clinical stakeholders via email, with written informed consent sought prior to surveys/interviews being undertaken.

### Recruitment

Recruitment is undertaken through clinicians in major treatment centres across Australia. With patient permission, clinicians are asked to directly refer eligible patients to the study team who then proceed with an informed consent process. A two-phase consent process is used for patient participants who are referred by a clinician: (1) written or verbal, where appropriate, permission to provide the patient’s contact details to the study team for follow-up and (2) written informed consent to take part in the study.

Additionally, men may self-refer having identified the study through media promotion and PCa support groups. In this case, potential participants contact the research team directly and provide written informed consent after being screened for eligibility.

Based on our experience with previous interventions in similar cohorts,^29–31^ and active participation of our project partners, we anticipate a recruitment period of 18 months to randomise 236 patients.

### Randomisation

Randomisation to study group condition occurs following receipt of baseline assessments (figure 2). Randomisation occurs in varying block sizes of 4, 6 and 8 (to ensure an unpredictable allocation sequence with equal numbers of men in each treatment group at the completion of each block) with no stratification factors. The randomisation sequence is undertaken by the project manager and concealed from investigators. Project staff tracking assessments (data analysts) will be blinded to condition.

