## Introduction

Prostate cancer (PCa) is the most common cancer diagnosed in Australia.^1^ While men are living longer following diagnosis, longitudinal research has characterised a subgroup of 35%–40% of men who experience long-term decrements in health-related quality of life (HR-QoL).^2^ In particular, men who are on androgen deprivation therapy (ADT) experience consistently poorer physical and mental HR-QoL over the long term.^2–6^

While ADT is effective in treating PCa and increasing survival, it is associated with multiple, often debilitating side effects, which manifest as changes in physical, cognitive, social and sexual functioning.^3 7–9^ Iatrogenic effects may include mood disturbances, increased fat mass, body feminisation, cognitive decline, functional impairment, frailty, fatigue and sexual dysfunction.^3 4 6–10^ ADT also increases the risk of developing new comorbidities, including cardiovascular conditions, diabetes, sarcopenia and osteoporosis.^11^ Compared with men receiving other treatments, those undergoing ADT report poorer HR-QoL and higher levels of psychological distress, including depression, anxiety, relationship changes, cognitive and affective symptoms, and sleep disturbances.^3 4 6–9 12^ The prevalence of psychological distress in PCa survivors is reported to be between 11% and 27%,^13^ and regardless of other treatments, receiving ADT is predictive of higher distress.^12^ Further, men undergoing ADT have an increased risk of suicide compared with those who do not, particularly in older men and in the first 6 months postdiagnosis.^14^ Unmet supportive care needs are highly prevalent in these men, with unmet physical, psychological, sexual, existential and informational^12 15^ needs that persist at 15 years postdiagnosis.^16^ Over one-third (37%) of men with PCa will report at least one long-term unmet supportive care need particularly at the start of treatment when side effects are new or unknown and HR-QoL is first impacted.^16^ This is of particular concern for men receiving ADT who report feeling unprepared to manage substantial treatment side effects that impact on quality of life.^17^ Further, despite routine clinical follow-up, men receiving ADT rarely receive tailored person-centred interventions in a timely manner, adversely impacting HR-QoL with poor management of side effects and self-efficacy.^12 15^ Men treated with ADT are a vulnerable high-need patient group for whom evidence-based survivorship care is crucial.

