## Methods and analysis

### Study design

A type 1 effectiveness-implementation hybrid randomised trial^24^ of a nurse-led survivorship care intervention (PCEssentials), relative to usual care, for improving HR-QoL in men with PCa undergoing ADT. A concurrent process evaluation will determine the effectiveness of intervention delivery, and the potential for implementation at scale. The study design has been guided by the Consolidated Standards of Reporting Trials (CONSORT) criteria.^26^

There are four key study time points:

T1—baseline: prior to randomisation.T2—3 months postrecruitment.T3—6 months postrecruitment.T4—12 months postrecruitment.

This study will be undertaken in accordance with the National Statement on Ethical Conduct in Human Research (2007—updated 2018)^27^ and the Australian Code for the Responsible Conduct of Research (2018).^28^ The study commenced in January 2022 on receiving ethics approval, with a planned end date of August 2026.

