### Research population

There are two research populations for this study:

Patient participants (n=236): Australian men (aged 18 years or over) diagnosed with PCa commencing, or within 3 months of having commenced, ADT.Process evaluation participants (n=148): Study stakeholders (n=30) who are directly involved in study delivery and/or translation into clinical practice, including participating service managers, recruiting clinicians, nurses delivering the intervention, health professionals and patient participants in the intervention group (n=118). While all participants in the intervention group will complete programme acceptability assessments at two study time points (T1 and T3), approximately 20 of these patient participants will be purposively selected/invited to take part in a semistructured interview (T3) to explore their experiences of the intervention. Purposive sampling will ensure a patient subgroup with maximum diversity (eg, based on age, background, location, partnered or unpartnered). We anticipate reaching data saturation for the process evaluation with this number of participants.

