### Inclusion criteria

Men recruited to the study will (1) have been diagnosed with PCa and be commencing, or within 3 months of having commenced ADT, and expected (based on clinical information) to be on ADT for a minimum continuous period of 12 months; (2) are able to read and speak English; (3) are able to give written informed consent; (4) have no history of head injury, dementia or psychiatric illness; (5) have no other concurrent cancer and (6) have mobile and/or landline phone access.

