### Research project procedures

#### Intervention

Following referral (clinician or self) to the study team, research staff screen potential participants for eligibility and conduct an informed consent process (figure 2). Once eligibility is confirmed, and written informed consent received, participants receive the baseline assessments (T1) via mail. On return of T1 assessments, the study team randomises participants into the intervention or minimally enhanced usual care (‘usual care’) group.

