### Research outcomes and measurement tools

Previously validated and reliable patient-reported outcome assessments are administered by mail to men at four time points: baseline/recruitment (T1), 3 months (T2), 6 months (T3) and 12 months (T4) after recruitment. Primary outcomes are HR-QoL and self-efficacy. Secondary outcomes include global psychological distress, insomnia, fatigue and life satisfaction. Demographic moderators/disease variables (eg, cancer grade, stage, time since diagnosis, time since treatment) and a health service use diary are self-reported. Assessments are self-reports with pen and paper.

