#### Intervention effectiveness

The study is a two-arm randomised controlled trial with repeated assessments across time and with continuous primary outcome variables. Recruitment bias will be assessed by comparing sociodemographic and clinical variables for consenters with non-consenters using t-tests (or Mann-Whitney U tests) for continuous variables and χ^2^ tests for categorical variables. Possible differential attrition will be assessed by comparing baseline characteristics of drop-outs and continuing participants using t-tests (or Mann-Whitney U tests if appropriate) for continuous variables and χ^2^ tests for categorical variables. Intention-to-treat analyses will be conducted. Between-group mean differences in change from baseline outcome scores at 3, 6 and 12 months will be analysed by fitting mixed effects regression models. Intervention (intervention/usual care) will be included as the main effect. Indicators for participants will be included as a random effect to account for the non-independence of repeated observations from the same individual. Sensitivity analysis will assess the effects of attrition. Mixed effects models with maximum likelihood estimation minimise bias that may arise from ignoring missing observations, and use all available data, thereby maximising statistical power to detect effects. The mean and 95% CI will be calculated for satisfaction with the intervention. Missing data will be examined for patterns of missingness and addressed with the appropriate multiple imputation methods, if required. The investigator team includes a dedicated biostatistician who will undertake analyses.

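### Time on ADT at baseline varies by design but has no place in the randomisation or in the effectiveness model as described; pre-specifying it as a covariate would recover a little precision

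*Protocol article*

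**What the plan says.** All references are to the protocol article.

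- **Entry window.** Research population describes men "diagnosed with PCa commencing, or within 3 months of having commenced, ADT". Inclusion criteria gives the same window and adds an expected minimum of 12 continuous months on ADT.
- **Timing of baseline.** Study design has "T1—baseline: prior to randomisation". Under Intervention: "Once eligibility is confirmed, and written informed consent received, participants receive the baseline assessments (T1) via mail". Randomisation follows return of the forms. No limit ties T1 to the start of ADT.
- **Follow-up clock.** Research outcomes and measurement tools sets the assessments at "baseline/recruitment (T1), 3 months (T2), 6 months (T3) and 12 months (T4) after recruitment".
- **Randomisation.** Blocks of 4, 6 and 8 are used, "with equal numbers of men in each treatment group at the completion of each block) with no stratification factors".
- **Effectiveness model.** Mixed models are fitted to change from baseline at 3, 6 and 12 months. "Intervention (intervention/usual care) will be included as the main effect", and participant is a random effect. No covariate is named.
- **Data collected.** Time since treatment is listed among the self-reported moderators and disease variables, but the effectiveness section gives it no role.
- **Background.** The Introduction says supportive care needs arise "particularly at the start of treatment when side effects are new or unknown and HR-QoL is first impacted".

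**The concern.** The entry window spans the period in which, on the article's own account, HR-QoL first suffers. A man just starting ADT may give a baseline that precedes most treatment effects. A man enrolled 3 months in may give a baseline that already contains some of them. Because visits run from recruitment, T2 falls at about 3 months of ADT for the first man (0 + 3) and about 6 months for the second (3 + 3). Their expected changes from baseline under usual care plausibly differ.

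Adjusting for the T1 score does not fully deal with this, since two men with the same score can be at different points in their course on ADT. What is at stake is precision. Variation that could be explained by a value known before randomisation stays in the residual, and a chance difference between the arms in time on ADT goes uncorrected.

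**Working it through.** **1. The plan's own sample size.** Inputs from Statistical considerations and data analysis: d = 0.40, 80% power, alpha 0.05, 15% attrition.

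- Normal approximation: n per arm = 2 × (1.96 + 0.842)² / 0.40² = 98.1, rounded up to 99, as stated. Two-sided alpha is needed; one-sided gives 78.
- Attrition: 99 / 0.85 = 116.5, so 117 per arm and 234 in total. The t-test solution is 99.08, rounded up to 100; 100 / 0.85 = 117.6, so 118 per arm and 236, as stated.

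The point disputes none of these figures. The article attaches d = 0.40 to psychological distress at 12 months, so here it serves only as a yardstick.

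**2. Assumptions.** The article gives neither the share of men not yet on ADT at T1 nor the size of any difference in change. Assume:

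- a share p = 0.5;
- a difference f in mean change between men not yet on ADT and men already on it of 0.2 to 0.5 SD, in units of the SD within those groups;
- one visit, analysed as a comparison of mean change, with 99 men per arm.

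**3. Loss of precision.** SD of change ignoring time on ADT = √(1 + p(1 − p)f²). Power = Φ(0.40 / (SD × √(2/99)) − 1.96). With f = 0 this is 80.4%.

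**4. Chance imbalance.** SE of the between-arm difference in share = √(2 × 0.5 × 0.5 / 99) = 0.071, so the 95% range is ±13.9 percentage points. Shift in the estimate = 0.139 × f.

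| f (SD) | SD of change | Power, unadjusted | n per arm for 80% | 95% range of shift (SD) |
|---|---|---|---|---|
| 0.2 | 1.005 | 80.0% | 100 | ±0.028 |
| 0.3 | 1.011 | 79.5% | 101 | ±0.042 |
| 0.5 | 1.031 | 77.9% | 105 | ±0.070 |

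With all 118 men per arm the imbalance range is ±12.8 points and the shift ±0.026 to ±0.064 SD. With a share of 30% or 70% at 99 per arm, the imbalance range is also ±12.8 points. If f were as large as 0.8 SD, power would be 74.3% and the shift ±0.11 SD.

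**5. Scale.** The 95% half-width of the treatment difference at 99 per arm is 1.96 × √(2/99) = 0.279 SD with f = 0, and 0.279 × 1.031 = 0.287 SD with f = 0.5. Steps 3 and 4 are two views of one quantity: the unadjusted standard error already contains the chance shift, so the losses do not add up.

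**6. Validity.** In 20,000 simulated trials with f = 0.5 and unstratified allocation, mean bias was about 0 (−0.0007 SD), type I error 5.0% and power 77%.

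**7. Gain from adjusting.** If 0.40 is instead read on the total SD, adjustment raises power from 80.4% to 80.7% (f = 0.2) or 82.7% (f = 0.5).

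**The case against.** The strongest reply is that this is a covariate list, which an article usually leaves to the SAP, and the SAP is not shown. The model paragraph is plainly condensed: it promises contrasts at three visits without naming a visit term, so naming only intervention does not show that nothing else will be fitted. Listing time since treatment among moderators also hints at some analytic use. Unstratified blocked randomisation of 236 men is a legitimate choice. All of this stands, and it keeps the point small. In the other direction, the Cost–utility analysis section does name its adjustment variables, while the effectiveness section names none.

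A reader might also infer more than the article supports:

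- **That the treatment estimate is biased.** Time on ADT is fixed before randomisation and balanced in expectation. What remains is chance error, which the standard error covers.
- **That the fall is steepest in the first 3 months.** The Introduction gives no slope or size. Its remark concerns men with prostate cancer in general and their unmet needs, and it also describes poorer HR-QoL on ADT over the long term.
- **That baselines are taken later than 3 months into ADT.** Entry is capped at 3 months. A later T1 is possible only because the mailing step has no stated time limit. Equally, that some T1 forms precede the first ADT treatment is inferred from the word commencing.
- **That the model excludes covariates.** The text is silent; it does not rule them out.

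**Conclusion.** The point holds as an inexpensive improvement, not as a fault in the validity of the trial. Time on ADT at T1 varies by design, plausibly predicts change in HR-QoL, is available before randomisation, and is used neither in allocation nor in the effectiveness model as described. With half the men not yet on ADT and a 0.2 to 0.5 SD difference in mean change, leaving it out costs about 0 to 2 points of power against the nominal 80%, and leaves a 95% range of chance shift of about ±0.03 to ±0.07 SD, or 7% to 18% of d = 0.40 at its edges. Both inputs are assumptions. The effect is probably most relevant at 3 months and weaker at 12. If the SAP already contains such a term, the point is met.

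**What to change.** Leave the randomisation and the total of 236 unchanged. Before the analysis, pre-specify time on ADT at T1 and its interaction with visit as baseline covariates in the mixed model for each primary outcome, alongside the baseline score.

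Code it only from what is known at T1: an indicator for ADT not yet started, plus months since start, set to zero for men who have not started. Avoid negative months for those men, because they would depend on a start date that comes after T1. Record the ADT start date at the eligibility screen, where ADT timing has to be established anyway; the self-reported time since treatment may not refer to ADT.

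The cost is a few degrees of freedom: two terms across three visits make at most 2 × 3 = 6 coefficients per outcome. Fixing the term in advance also avoids a post hoc decision should an imbalance appear.

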### Research project process

#### Patients

Patient-reported outcomes and experience assessments are completed at each study time point (T1–T4). Following informed consent, participants are sent the T1 assessments for completion. On receipt of completed T1 assessments by the research team, participants are randomised into either (1) minimally enhanced usual care (control) or (2) nurse-led survivorship care: PCEssentials (intervention group).

##### Minimally enhanced usual care

Standard management, minimally enhanced with evidence-based patient education materials about the use of ADT to treat PCa and information about free telephone-based cancer information and support services in the participant’s home state.

##### Nurse-led survivorship care (PCEssentials)

The nurse-led intervention is telephone delivered over five sessions by trained PCa specialist nurses, guided by manualised intervention protocols and supervised by an experienced PCa specialist nurse and a health psychologist with extensive experience in PCa supportive care. The intervention includes five modules covering: psychoeducation with tailored distress management strategies; decision support; treatment education with self-management and skills training for symptom effects, including exercise/physical activity resources and support and communicating with health professionals including a referral pathway to their general practitioner for chronic disease management.

A problem-solving approach that supports personal agency underpins each component,^20^ with the first four sessions to be delivered by telephone over 3 months, and an additional booster session 5 months after the initial session module has been completed. A problem-solving approach^32^ that is responsive to masculine models of coping and life stage was chosen as the underlying mechanism of support to enhance personal agency.

Men with PCa experience improved psychological outcomes when they engage in approach coping that addresses the threats associated with their cancer,^33^ and active problem solving is consistent with male values around strength, self-reliance and action.^34^ Problem-solving therapy (PST) has been found to be effective in reducing depression and disability in older people (>60 years of age) with chronic illness.^32^ Our intervention targets include major challenges identified by men (eg, psychological distress, disease and treatment effects, communicating with health professionals) and applies PST to enhance men’s personal agency in defining and formulating the nature of their specific problems, generating potential solutions, systematically evaluating possible consequences of solutions and selecting an appropriate solution, and monitoring solution outcomes. A self-help survivorship resource that addresses key PCa-related challenges with evidence-based coping strategies is provided and this connects directly to the nurse-led intervention session content.^35^

Distress screening and problem identification occur at each session using the Distress Thermometer and are integrated with distress and symptom management strategies.^36^ The booster session checks participant progress, reinforces self-management skills, and troubleshoots concerns that may have persisted.

A home-based physical exercise programme is offered, where men are encouraged to seek at least one planning session with an AEP within their treatment team, accessed by telephone or internet. The nurse specialist encourages exercise maintenance, including aerobic and resistance training as per the Australian Exercise Medicine for Cancer guidelines with referral to an AEP, if required.^37^

Men have identified that the PCa specialist nurse/clinical nurse is highly acceptable as the provider of survivorship care, an approach described as the most efficient in terms of use and resources and being suitable for most care settings.^38^ Tele-based interventions are also highly acceptable to men with PCa (85% consent rate^22^), are accessible for patients who are very unwell,^39^ have been shown to be an effective delivery method for PST^32^ and in advanced disease show low attrition rates compared with face-to-face delivery.^20^ This delivery method is also applicable to geographically dispersed and vulnerable populations with high potential for population-based translation.

#### Process evaluation

Process assessments are collected via: (1) surveys using the programme acceptability: acceptability of intervention measure (AIM), intervention appropriateness measure (IAM) and feasibility of intervention measure (FIM)^40^ at T1 and T3 (patient participants) and when recruitment commences and ends (other stakeholders), as well as the Working Alliance Inventory-Short Revised (WAI-SR) scale^41^ at T3 (intervention group patient participants only); (2) semistructured interviews with stakeholders at T3 (patient participants) and when recruitment ends (other stakeholders) and (3) intervention fidelity and adherence assessments at multiple study time points, to identify barriers and facilitators to implementation, and determine if high intervention fidelity is achieved.

### Research outcomes and measurement tools

Previously validated and reliable patient-reported outcome assessments are administered by mail to men at four time points: baseline/recruitment (T1), 3 months (T2), 6 months (T3) and 12 months (T4) after recruitment. Primary outcomes are HR-QoL and self-efficacy. Secondary outcomes include global psychological distress, insomnia, fatigue and life satisfaction. Demographic moderators/disease variables (eg, cancer grade, stage, time since diagnosis, time since treatment) and a health service use diary are self-reported. Assessments are self-reports with pen and paper.

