### Primary hypothesis

We hypothesise that PCEssentials will be more cost-effective than usual care. Furthermore, relative to men receiving usual care at 3, 6 and 12 months after recruitment, men who receive PCEssentials will have: (1) higher HR-QoL, (2) increased self-efficacy, (3) less psychological distress and (4) improved sleep and lower fatigue.

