#### Primary outcomes

##### Health-related quality of life

The Functional Assessment of Cancer Therapy-Prostate^42^ assesses men’s disease-specific quality of life across five domains: physical, social/family, emotional, functional well-being and PCa-specific concerns.^42^ The Assessment of Quality of Life (AQoL-8D) instrument is used to derive health utility scores and general HR-QoL among patients. This tool has increased measurement sensitivity to psychosocial elements of health compared with other instruments since it comprises five psychosocial dimensions (mental health, happiness, coping, relationships and self-worth) and three physical dimensions (independent living, pain and senses).^43^ The physical function subscale from the Medical Outcomes Study Short-Form-36 questionnaire will be used as an indicator of patient-related physical functioning QoL.^44^ We recently reported improvements in physical function in PCa patients with advanced disease and bone metastases following an exercise intervention using this measure, and in those on ADT with localised disease.^45^

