##### Self-efficacy

The 11-item Cancer Survivorship Self-Efficacy Scale^46^ assesses self-efficacy to manage problems arising from cancer and its treatment specifically.

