### Statistical considerations and data analysis

Recent meta-analyses conclude that individually focused psychological interventions should produce improvements in psychological distress of at least a medium effect size (d=0.40) that will be clinically meaningful.^53^ To see an effect of this size or greater in our primary outcome, psychological distress at 12 months, with 80% power and alpha=0.05, we will require 99 participants in each group to complete the intervention. Assuming 15% attrition, we will recruit 236 patients to the study (118 patients per group).

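### The primary endpoint is badly fixed: four instruments are listed as primary, no HR-QoL scale leads, no visit is ranked first, and the only alpha and time point are set for an outcome classed as secondary

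*Protocol article*

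**What the plan says.** All references are to the protocol article.

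- **Outcome list.** Research outcomes and measurement tools: "Primary outcomes are HR-QoL and self-efficacy". The Abstract agrees. Both place psychological distress among the secondary outcomes, as does the Secondary outcomes section.
- **HR-QoL instruments, under Primary outcomes.** There are three. "The Functional Assessment of Cancer Therapy-Prostate^42^ assesses men’s disease-specific quality of life across five domains". "The Assessment of Quality of Life (AQoL-8D) instrument is used to derive health utility scores and general HR-QoL among patients". "The physical function subscale from the Medical Outcomes Study Short-Form-36 questionnaire will be used as an indicator of patient-related physical functioning QoL". None is put ahead of the others.
- **Self-efficacy instrument, under Primary outcomes.** There is one: "The 11-item Cancer Survivorship Self-Efficacy Scale^46^ assesses self-efficacy to manage problems arising from cancer and its treatment specifically".
- **Visits.** The Primary hypothesis compares the groups "relative to men receiving usual care at 3, 6 and 12 months after recruitment". Intervention effectiveness likewise analyses between-group differences in change at all three visits. It also enters treatment group as the main effect.
- **Alpha and power.** Statistical considerations and data analysis sizes the trial "with 80% power and alpha=0.05" for d=0.40. That paragraph calls 12-month psychological distress the primary outcome.
- **Scope of the hypothesis.** The Primary hypothesis also covers cost-effectiveness, distress, sleep and fatigue.

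**The concern.** A confirmatory trial needs one identifiable comparison, or a defined set, on which its main claim stands. Here the one paragraph that brings together an outcome, a visit and an alpha does so for an outcome that is not on the primary list. The outcomes that are on the list have no visit or alpha of their own, and HR-QoL has three candidate scales.

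The same data could therefore be called positive or negative depending on which scale and visit are put forward after the results are known. Mixed results, such as FACT-P favourable at 3 months and AQoL-8D null at 12, could not be turned into one conclusion. The false-positive rate of the main claim cannot be stated either, because it depends on a choice that the article does not make.

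**Working it through.** **1. Reproduce the plan's figure.** Inputs from Statistical considerations and data analysis: d=0.40, power 80%, alpha 0.05, 15% attrition.

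n per group = 2(1.960 + 0.842)² / 0.40² = 2 × 7.85 / 0.16 ≈ 98.1, rounded up to 99. This matches the stated 99. The exact t-test solution is 99.08. A one-sided test would need 78, so the stated alpha is two-sided. For attrition, 99 / 0.85 = 116.5, so 117 per group against the stated 118, a small rounding up. The sample size is correct for one comparison at one visit.

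**2. Count the comparisons.**

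- One test per domain: 2.
- One test per instrument, which is how the main-effect wording can be read: 3 + 1 = 4.
- Every instrument at every visit, as the hypothesis and the analysis section can be read: 4 × 3 = 12.

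**3. Chance of at least one false positive if any single result suffices.** With k independent tests, each at two-sided 0.05, it is 1 − 0.95^k:

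- k=2: 1 − 0.9025 = 9.8%
- k=4: 1 − 0.8145 = 18.5%
- k=12: 1 − 0.5404 = 46.0%

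The scales and visits will be correlated, and the article gives no values, so the correlations here are assumptions. Simulating correlated normal test statistics (1,000,000 draws) gives the lower ends:

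| Tests | Assumed correlation | Any two-sided error |
|---|---|---|
| 2 | 0.7 | 8.3% |
| 4 | 0.7 between scales | 13.0% |
| 12 | 0.7 between scales, 0.8 between visits | 24.0% |

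The ranges are therefore about 8-10%, 13-18.5% and 24-46%.

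**4. Errors that favour the intervention only.** The benchmark for one test is 2.5%. Under independence:

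- Four tests: 1 − 0.975^4 = 9.6%
- Twelve tests: 1 − 0.975^12 = 26.2%

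Under the same correlations as in step 3, the simulated figures are 6.5% and 12.0%. The ranges are about 6.5-10% and 12-26%.

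**5. The opposite rule.** If every primary test must be significant, the chance of a false overall claim is at most that of a single test, so there is no inflation.

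**6. Cost of splitting alpha instead.** With 99 per group and d=0.40, power ≈ Φ(0.40 × √(99/2) − z) = Φ(2.814 − z).

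- Alpha 0.05: Φ(2.814 − 1.960) = 80%
- Alpha 0.025 (two domains): Φ(2.814 − 2.241) = 72%; the exact t-test gives 71%
- Alpha 0.0125 (four instruments): Φ(2.814 − 2.498) = 62%

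These use the d=0.40 that the article takes from evidence on distress. It offers no effect size for HR-QoL or self-efficacy.

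**The case against.** The tempting stronger reading is that the trial's false-positive rate is several times 5%. The documents do not support that as a flat statement. It assumes that one significant result on any scale at any visit counts as success, and the article states no such rule. The hypothesis is in fact worded as a list joined by *and*, and under an all-must-succeed rule nothing is inflated.

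Four further points on the other side:

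- **Twelve is not a minimum.** The main-effect wording allows one test per instrument, which makes four.
- **A visit is named.** The sample-size paragraph names 12 months. It does so only for distress, so it remains true that neither listed primary outcome has a visit of its own.
- **Testing order and adjustment may sit in the SAP.** The SAP is not shown, so their absence from the article is not a fault in itself.
- **The largest percentages are extreme.** The 46% figure needs zero correlation between repeated scores of the same man, whereas the planned model allows for exactly that dependence. For a false claim of benefit, only favourable errors count.

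Cost-effectiveness does not add to the count either: it is assessed by an incremental ratio with bootstrapping, not by a test at 0.05.

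All of this limits the size of the point and makes it conditional. It does not remove it. Which outcome is primary is protocol content. This article does fix it, in a way that leaves several candidates and conflicts with its own sample-size paragraph.

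**Conclusion.** The point holds as a badly fixed primary endpoint. Four instruments stand under the primary heading without a lead HR-QoL scale, three visits are unranked, and the one comparison given an alpha and a visit is on an outcome classed as secondary in three places.

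The effect on error is conditional. If any one primary result may carry the claim, the two-sided false-positive chance runs from about 8% (one test per domain, correlated) to 46% (twelve independent tests), with 13-18.5% for one test per instrument. Counting only errors in the intervention's favour, it is about 6.5-10% for four tests and 12-26% for twelve, against 2.5% for one. These figures assume between-scale correlations of 0 to 0.7 and between-visit correlations of 0 to 0.8. The arithmetic of the sample size is sound, but it is attached to the wrong outcome.

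**What to change.** Before unblinding:

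1. Name one primary HR-QoL scale at one visit, tested at two-sided 0.05. FACT-P total at 12 months is one reasonable choice: it is disease-specific, fits Aim 1, which concerns HR-QoL, and keeps the visit used for sizing. Other choices are defensible; the essential step is to name one.
2. Test the self-efficacy scale at 12 months at 0.05 only if the first test is significant. This fixed sequence controls the error over both without dividing alpha.
3. Make the other HR-QoL scales and the 3- and 6-month contrasts secondary, reported as estimates with 95% confidence intervals.
4. Limit the primary hypothesis to these two outcomes.
5. Correct the sample-size paragraph so that it names the chosen primary outcome. Either justify d=0.40 for that outcome or say plainly that the 80% power refers to distress. Moving to FACT-P at 12 months matches only the month of the present power statement, not its outcome.

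The change is wording in the protocol and SAP, and the fixed sequence itself calls for no extra patients. The price is that fewer results can be called primary, and self-efficacy cannot be confirmed if HR-QoL fails.
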